### Data analysis

For our primary outcome analysis, we compare odds ratios for STI incidence and IPV perpetration in the past 12 months, across arms at 30 months for both behavioral and STI outcomes using SAS SURVEYLOGISTIC version 9.4 [69] to adjust for correlation due to clustering within camps and incorporate both the complex nature of sample selection and weighting. Controls for covariates will be introduced where necessary. In the event that program effects are identified, we will assess the degree to which hope, future orientation, and structural characteristics of the networks mediate the impact of the intervention on STI and IPV. Indirect (mediated) effects of the intervention will be calculated using Mplus and assessed for significance using construction of Monte Carlo confidence intervals [70].

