## Methods/Design

### Research design and methods

#### Overview

Vijana Vijiweni II is a cluster-randomized controlled trial, with the unit of randomization being camps. The trial tests whether men in camps randomized to a combined microfinance and peer health leadership intervention have less incident sexually transmitted infections (Neisseria gonorrhea (NG), Chlamydia trachomatis (CT), and Trichomonas vaginalis (TV) and report less past-year perpetration of physical and/or sexual violence against female sexual partners compared to men in the control camps who will get a delayed intervention. Sixty camps are enrolled in the trial and half are randomly assigned to the intervention arm and half to the control arm. All members who meet the study eligibility criteria (detailed below) are offered enrollment in the trial. Behavioral and biological data are collected at baseline, which is completed two months prior to initiating the intervention, and endline which occurs 30 months post intervention launch. We are also conducting a midline behavioral assessment at 12-months post intervention launch. The intervention runs for a period of 2 years.

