#### Selection and random assignment of camps for the trial

Due to the density of geographically proximal camps (see Fig. 2), we used a three step, probability based sampling method that reduced the possibility of contamination effects to randomly select 60 eligible camps in to the trial: (1) field staff familiar with the physical geography of wards and camps assigned geographically proximal camps to groups containing between 1–6 camps on ArcGIS generated maps; (2) probability proportionate to size with minimal replacement sampling of groups was conducted using SAS Survey Select Procedure; (3) simple random selection of camps within groups selected was completed. By using minimal replacement, groups containing greater numbers of camps with high membership numbers could be selected more than once. In such an instance, the number of times a group was selected equaled the number of camps selected randomly from that group. The 60 randomly selected camps were first randomized into two sets of 30 camps. Multiple camps selected from within the same geographically proximally group were assigned to the same set. Treatment condition of these two sets was then randomly, and transparently, assigned at a CAB meeting following completion of baseline data collection. At the CAB meeting, the two sets were assigned numbers one and two. Papers with these numbers were then put in separate but identical balloons, and three other papers that stated “try again” in three other identical baloons. The CAB decided that the first number to be selected would be assigned to the intervention condition. One CAB member was selected to be the one to randomly pick and pop the balloons until a number was found.

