### Sample size determination

The choice of 60 camps randomized into two groups is based upon evidence generated in our previous study and likely incidence estimates available from published studies with similar populations in Tanzania and other countries in Africa [10, 68]. We estimated average camp sizes of 26.4 men and expected to successfully enroll approximately 80 % of these men into our trial at baseline. 90 % of the men were expected to be sexually active at baseline. Any STI incidence (NG, CT, or TV) was used as the primary outcome measure and sexual and/or physical IPV perpetration was used as the primary behavioral outcome measures. Based upon our previous study we computed camp intraclass correlation (ICC) estimates between 0.00 and 0.01 for sexually transmitted diseases and 0.032 for behavioral measures. Given anticipated average camp sizes and ICC estimates we inflated sample size estimates assuming simple random sampling with design effects ranging from 1.4 to 2.3. All sample estimates assumed an attrition of 20 %. Given a sample size of 890 sexually active males and 999 total males in 60 camps at our 30-month assessment, we will have 80 % power (2-sided, α = 0.05) to detect protective effects of the intervention (OR) of .57 for STI incidence and .65 for perpetration of sexual or physical IPV among sexually active men. Statistical power to detect mediation is expected to be high based on the simulation results of Fritz and MacKinnon where a total sample size of 539 was sufficient for .80 power to detect the most conservative simulated mediation effect.

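### Camps from one geographic group were allocated together, but the primary analysis names only the camp as cluster; if the camp is used, standard errors are likely too small, mainly for IPV

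*Protocol article*

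**What the plan says.** The Overview describes a cluster-randomised trial "with the unit of randomization being camps".

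The section on selection and random assignment of camps describes a more restricted procedure. Field staff "assigned geographically proximal camps to groups containing between 1–6 camps". Then "probability proportionate to size with minimal replacement sampling of groups was conducted using SAS Survey Select Procedure", followed by simple random selection of camps inside the chosen groups. The section adds that "groups containing greater numbers of camps with high membership numbers could be selected more than once". On allocation it says "The 60 randomly selected camps were first randomized into two sets of 30 camps", with this restriction: "Multiple camps selected from within the same geographically proximally group were assigned to the same set". One of the two sets was then drawn for the intervention.

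Under Sample size determination the only correlation considered is at camp level: "we computed camp intraclass correlation (ICC) estimates between 0.00 and 0.01 for sexually transmitted diseases and 0.032 for behavioral measures".

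Under Data analysis, both primary outcomes are compared at 30 months with SAS SURVEYLOGISTIC "to adjust for correlation due to clustering within camps and incorporate both the complex nature of sample selection and weighting".

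**The concern.** Camps that must share an arm are not randomised independently of each other. For any group that supplied two or more camps, the group is what was allocated. Where a group supplied a single camp, group and camp coincide. The group is also the primary sampling unit of the selection design. The Overview does not mention this level, and the sample size and analysis sections name only the camp.

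This matters because the SURVEYLOGISTIC variance estimator treats the units in its CLUSTER statement as independent. With the camp in that statement, neighbouring camps in the same arm count as separate evidence, and sampling weights do not change that. If men in neighbouring camps resemble each other, the shared component adds to the variance of the treatment contrast but is left out of its standard error. Confidence intervals would then be too narrow and the type I error above 5%. The endpoint with the larger ICC, IPV perpetration, would be affected most.

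**Working it through.** **Inputs from the protocol.** There are 60 trial camps, with 890 sexually active men expected at 30 months, so m = 890/60 = 14.83 men per camp. The camp ICC is 0.032 for behavioural measures and 0.00 to 0.01 for STI. The allocation section gives 1 to 6 camps per geographic group. The PLACE assessment section gives 172 eligible camps.

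**Not given, so assumed.** Two quantities are missing: the number of groups that supplied the 60 camps, and the correlation ρg between men in different camps of one group.

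**The plan's own figures.** The stated 80% power cannot be reproduced, because no control-arm rates are given. The camp-level design effect follows from the stated ICCs as DEcamp = 1 + (m − 1) × ICC:
- IPV: 1 + 13.83 × 0.032 = 1.44
- STI at ICC 0.01: 1 + 13.83 × 0.01 = 1.14

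**Step 1: camps per group.** With 60 draws from 172 eligible camps, a camp of average size expects 60/172 = 0.349 draws, and a group of s such camps expects 0.349 × s. Sampling with minimal replacement limits a group's draws to that number rounded down or up. Assume that group sizes 1 to 6 are equally common, camps are of equal size, and groups were formed from the eligible camps.
- Expected draws for s = 1 to 6: 0.349, 0.698, 1.047, 1.395, 1.744, 2.093 (sum 7.326).
- Probability of at least one draw: 0.349, 0.698, 1, 1, 1, 1 (sum 5.047).
- Mean camps per selected group: 7.326/5.047 = 1.45, so about 60/1.45 ≈ 41 groups.
- Expected squared draws: 0.349, 0.698, 1.140, 2.186, 3.233, 4.465 (sum 12.07).
- Size-weighted camps per group: k = 12.07/7.326 ≈ 1.65.

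**Step 2: effect of leaving out the group level.**
- DEgroup = DEcamp + m × (k − 1) × ρg
- Standard error ratio R = √(DEgroup/DEcamp)
- True level = 2 × [1 − Φ(1.96/R)]
- Power = Φ((1.96 + 0.842)/R − 1.96), starting from a nominal 80%

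At k = 1.65, the added term for IPV with half the ICC shared is 14.83 × 0.65 × 0.016 = 0.154. The other rows follow in the same way.

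| Outcome | Share of camp ICC common to group | DEcamp | DEgroup | R | True level | Power |
|---|---|---|---|---|---|---|
| IPV, ICC 0.032 | half | 1.44 | 1.60 | 1.05 | 6.2% | 76% |
| IPV, ICC 0.032 | all | 1.44 | 1.75 | 1.10 | 7.5% | 72% |
| STI, ICC 0.01 | half | 1.14 | 1.19 | 1.02 | 5.5% | 78% |
| STI, ICC 0.01 | all | 1.14 | 1.23 | 1.04 | 6.0% | 77% |
| STI, ICC 0.00 | any | 1.00 | 1.00 | 1.00 | 5.0% | 80% |

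**Step 3: range.** With k = 1.2 and a quarter of the ICC shared, the IPV level is 5.2%. With k = 2 it is 6.9% (half shared) or 8.9% (all shared). With k = 1 or ρg = 0 nothing changes. The two-camp case is near the top of what the scheme allows: even a frame made only of six-camp groups would average about 2.1 camps per group.

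**The case against.** The strongest reply is that the Data analysis sentence does not stop at camps. It also promises to account for the sample selection, whose first stage is the geographic group. In SURVEYLOGISTIC that would normally mean declaring the first-stage unit as the cluster, and since camps nest in groups, camp correlation would be covered too. The exact CLUSTER variable may also be left to an analysis plan that is not shown. This stands to the extent that a reader might infer that the plan definitely clusters on the camp alone, and the text does not establish that. It does not remove the point. The one correlation level the sentence names is the camp, and the Overview's unit of randomisation conflicts with the allocation section whichever cluster is intended.

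A second reply is that the size is unknown, and that also stands. Positive correlation between neighbouring camps is plausible but not shown. The Discussion treats proximity as a risk of information passing between arms, which is spillover of the intervention and not evidence of correlated outcomes. The case in which all the ICC is shared leaves no camp-specific component, which sits badly with the protocol's picture of cohesive camps.

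Two stronger readings are tempting. One is that levels reach 13%, which needs three camps per group with all the correlation shared. Sixty draws from 172 eligible camps do not fit that, since a six-camp group of average-sized camps expects only about 2.1 draws. The other is that tossing two pre-formed sets leaves just two randomised units. It does not, because the sets were themselves formed at random.

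**Conclusion.** The point holds as an inconsistency in the stated unit of randomisation and an unspecified group level in the primary analysis. The consequence is conditional: standard errors are likely too small if the camp is used as the cluster, some groups supplied several camps, and neighbouring camps are positively correlated.

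On the working assumptions (k about 1.65, half to all of the camp ICC shared), the understatement is modest for IPV and small for STI at the upper stated ICC. It vanishes at an STI ICC of 0 or if every group supplied one camp. A reader might infer a demonstrated type I error above 5% for both primary endpoints, but the protocol does not support that. The correction is still worth making before analysis, because it concerns the validity of the primary tests and costs almost nothing.

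**What to change.** 1. In Data analysis, name the geographic group as the SURVEYLOGISTIC cluster for both primary outcomes, with degrees of freedom based on the number of groups (for example groups minus 2, about 39 if there are 41 groups, against 58 for 60 camps).
2. In the Overview, say that geographic groups of one or more camps were randomised.
3. Report how many groups supplied the 60 camps, by arm.
4. Keep camp-level clustering as a sensitivity analysis.

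The group identifier must already exist, since sampling and allocation both used it. The cost is one line of code, a sentence or two of text, and slightly wider intervals.

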### Study assessments

Study assessments are conducted at baseline, 12-months post-intervention launch and at 30-months post-intervention. Behavioral surveys are collected at each assessment, and biological samples are collected at baseline and 30-month post-intervention only. Prior to the first assessment participants are asked for consent to participate in the study, which the participant provides by signing a consent form and writing their initials next to the assessments (behavioral, biological) to which they agree to participate. Participants must re-assent to participate in future behavioral assessments and consent to participate in biological assessment if not done at baseline. Behavioral surveys are conducted in field offices located in the study wards through computer-assisted personal interviews (CAPI) using tablet devices. Each interview is expected to take approximately 60–90 min to complete. Sixteen local interviewers, trained in human ethics, confidentiality, interviewing techniques, data collection methods, and use of CAPI devices, collect all behavioral data. To collect biological specimens, blood and urine samples are drawn from participants immediately after the behavioral survey is completed. To assess baseline prevalence of sexually transmitted infections (STIs), a subsample of 50 % of men that report ever having sex on their baseline survey are asked to provide a blood and urine specimen for HIV and STI tests. At the 30-month assessment, all men are asked to provide biological samples. Participants are refunded the equivalent of $3 for transport.

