### Measures

The primary endpoints to assess intervention impact are STI incidence and IPV perpetration. To assess STI incidence, we are using Qiagen Artus CT with in-house PCR to detect CT, Trichomonas vaginalis Real-TM test to detect TV, and 16 s rDNA PCR to detect NG. For the follow-up testing at 30 months we are using Multiplex PCR to detect CT and NG. Study participants who are identified with NG, CT, or TV are offered free treatment by a study clinician at the study site according to the standard of care in Tanzania specifically NG (Ceftriaxone), CT (Doxycycline), TV (Metronidazole). IPV perpetration is assessed using an adapted version of the World Health Organization violence against women instrument [63]. This tool measures psychological, physical, and sexual IPV perpetration. Participants are asked whether they have perpetrated any of 13 behaviorally specific violent acts, including 4 psychological acts, 4 physical acts and 3 sexually violent acts, against a current or former sexual partner. For those who say yes to ever having perpetrated a specific act of violence, they are asked to report how many times they perpetrated that act in the last 12 months. Response options included never, once, 2–3 times, 4–10 times, and more than 10 times. The responses to the frequency of physical and sexual IPV perpetration within the last 12 months are dichotomized such that a 0 represents no sexual/physical IPV perpetration and a 1 represents at least 1 act of sexual or physical IPV perpetration within the last 12 months. We are measuring gender norms with the gender-equitable men’s scale [36], as well as hope [64], future orientation [65], and perceived social support as mediators of the intervention’s effects. We are measuring camp-level social cohesion using five items adapted from a measure of social cohesion developed by Sampson, Raudenbush & Earls [66]. For example, participants are asked how strongly they agree with statements like “people in my camp are willing to help each other” and “the members of my camp share the same values.” In addition, we are collecting data on all social ties within each camp at multiple waves of data collection. We are using these complete network data to assess whether our intervention is mediated through the transformation of social network structures (e.g. structural cohesion [67]). Finally, we are also looking at HIV risk behaviors as secondary endpoints including unprotected sex, sexual partner concurrency, alcohol and other substance use.

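### The primary IPV model leaves its covariates open and does not name baseline IPV, although the same measure is collected before the condition is drawn

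*Protocol article*

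**What the plan says.** The primary analysis in the Data analysis section reads: "we compare odds ratios for STI incidence and IPV perpetration in the past 12 months, across arms at 30 months". It uses survey logistic regression to "adjust for correlation due to clustering within camps and incorporate both the complex nature of sample selection and weighting". The one statement on adjustment is "Controls for covariates will be introduced where necessary". Baseline IPV is neither named nor excluded.

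The Study assessments section says: "Behavioral surveys are collected at each assessment, and biological samples are collected at baseline and 30-month post-intervention only". The Measures section defines the IPV outcome as binary, where "a 1 represents at least 1 act of sexual or physical IPV perpetration within the last 12 months". The baseline survey therefore carries the endpoint itself, measured over the same recall period.

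The section on selection and random assignment of camps says that the condition of the two sets of 30 camps was drawn at a community advisory board meeting after baseline data collection was complete. It describes no stratification or matching on earlier IPV.

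STI differs. At baseline, "a subsample of 50 % of men that report ever having sex on their baseline survey are asked to provide a blood and urine specimen". A baseline value of that endpoint is missing for at least half of the men, so the point is confined to IPV.

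**The concern.** A baseline value of the endpoint is usually among its best predictors. In a trial with 30 camps per arm, using it removes part of the between-man variance and, if camps differ stably, part of the between-camp variance. A primary model that does not commit to it may give up precision that the data already held could provide.

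The second problem is the open clause. Without a named list or a criterion, the covariates can be settled once outcomes by arm are visible. A reader of the final result could not tell whether the adjusted or the unadjusted odds ratio was the one intended.

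**Working it through.** **1. The plan's own figure.** The Sample size determination section states 80% power (two-sided, α = 0.05) for OR 0.65, with 890 sexually active men in 60 camps, a behavioural ICC of 0.032 and design effects of 1.4 to 2.3. It gives no control IPV rate, so the 80% cannot be fully checked. With p₂ = o/(1 + o), o = 0.65·p₁/(1 − p₁) and n per arm = 445/DE:

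power = Φ{[(p₁ − p₂) − 1.96·√(2p̄(1 − p̄)/n)] / √[(p₁(1 − p₁) + p₂(1 − p₂))/n]}

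At the smallest stated DE (1.4), the highest power at any control rate is 77.3% (at p₁ = 0.554). With all 999 men and DE 1.4, the result is within 2 points of 80% for control rates of about 0.40 to 0.70. Power for IPV therefore has little or no slack.

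**2. Gain from baseline IPV.** Camp size is 890/60 = 14.83, so DE = 1 + 13.83 × 0.032 = 1.443 and n = 445/1.443 = 308.4 per arm. Adjusting for a baseline value with correlation r multiplies effective n by 1/(1 − r²), which is 1.04, 1.10, 1.19 and 1.33 for r = 0.2, 0.3, 0.4 and 0.5.

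The control rate and r are assumptions. The lowest rate, 0.238, borrows the survey figure in the Background for women in Dar es Salaam reporting physical violence in the last 12 months. It has a different reporter and a narrower definition than the endpoint, so it is only a reference point.

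| Control rate | Rate at OR 0.65 | No baseline | r = 0.2 | r = 0.3 | r = 0.4 | r = 0.5 |
|---|---|---|---|---|---|---|
| 0.238 | 0.169 | 57.0% | 58.7% | 61.0% | 64.5% | 69.4% |
| 0.30 | 0.218 | 64.4% | 66.2% | 68.5% | 72.0% | 76.8% |
| 0.40 | 0.302 | 72.0% | 73.8% | 76.0% | 79.3% | 83.6% |

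The gain is about 2 points at r = 0.2 and about 12 at r = 0.5.

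**3. Simulation.** This used 60 camps of 15 men, ICC 0.032, OR 0.65, logistic regression with camp-robust standard errors and 600 replicates per setting (Monte Carlo error about 2 points). Power without and with each man's baseline IPV, by observed baseline-to-endline correlation (phi):

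| Control rate | phi | Without | With |
|---|---|---|---|
| 0.24 | 0.21 | 63% | 68% |
| 0.24 | 0.31 | 61% | 69% |
| 0.24 | 0.47 | 58% | 77% |
| 0.35 | 0.23 | 75% | 80% |
| 0.35 | 0.33 | 71% | 81% |
| 0.35 | 0.49 | 70% | 87% |

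At phi near zero the gain was about 1 point. The simulation assumes the same camp effect at both times, which favours adjustment. Adding the camp mean changed power by at most about 2 points.

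**4. Cost of leaving the choice open.** Suppose the unadjusted and adjusted tests were both run and either could be reported. Taking their correlation under the null as √(1 − r²), the chance that at least one reaches p < 0.05 is 5.9% at r = 0.2, 6.9% at r = 0.4 and 7.3% at r = 0.5. This covers one optional covariate; an open list allows more.

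**The case against.** The strongest objection is that a journal article may leave the adjustment list to a full protocol or SAP, and neither is shown. That would dispose of a complaint about missing detail. It does not fully answer this one, because the article states a rule for the primary model and the rule is open. If an SAP already fixes the list, the article's sentence needs only to be aligned with it.

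Four stronger readings are tempting, and the document does not support them.

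- *The plan does not use baseline IPV.* The clause names nothing and excludes nothing, so baseline IPV could enter under it. Silence is not exclusion.
- *The model can be changed after unblinding.* No blinding is described, and the condition was drawn openly. The relevant moment is when outcomes are seen by arm. The article does not say when covariates are chosen.
- *A chance baseline gap could be as large as the target effect and would bias the result.* At an assumed 30% prevalence, with 629 men per arm and DE 1.64, the standard error of the baseline difference is √(2 × 0.3 × 0.7 × 1.64/629) = 0.033, a 95% range of about ±6.5 points. The target difference is 0.300 − 0.218 = 8.2 points (z = 2.48), so a gap that large has a probability of about 1%. Only part of it would carry over to 30 months. Chance imbalance is already part of the sampling error that the cluster-adjusted analysis reflects.
- *The STI model needs its own fixed covariates for the same reason.* The argument rests on a baseline value of the endpoint, which is not available for STI in most men. Nothing in the document supports a particular STI list.

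The objection that the gain is not known also stands in part: it cannot be sized from the document. The stated power was not based on adjustment, so no stated figure becomes wrong.

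**Conclusion.** The concern holds as a point about efficiency and pre-specification, not validity. The 30-month comparison without covariates is a valid analysis of a randomised trial. It is less precise than one using a pre-allocation measure of the endpoint, and the covariate clause leaves the primary IPV model open to choice.

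On the variance approximation the gain is about 2 to 12 power points for correlations of 0.2 to 0.5 at control rates of 0.238 to 0.40. The simulation reached 19 points (58% to 77%) with a persistent camp effect and phi 0.47, and showed about 1 point at phi near zero. The control rate, the correlation and the stability of camp effects are all assumed.

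One dependency should be confirmed. The section on selecting participants places completion of the rosters after random assignment, whereas the preceding section places the draw of the condition after baseline. The Retention section says rosters were collected before the baseline assessment. The three fit together if the earlier assignment means only the split into two unlabelled sets. The sponsor should confirm this, because the case for baseline IPV rests on its having been measured before the condition was known.

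**What to change.** For the IPV endpoint, replace the open clause with a covariate list fixed and dated before 30-month outcomes are seen by arm:

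- each man's baseline past-12-month physical or sexual IPV, in three categories: none, any, and no sexual partner yet;
- optionally, the camp-mean baseline IPV.

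The third category is needed because the sample size section expects only 90% of men to be sexually active at baseline. A 0/1 term would merge men who have had no partner with partnered men who reported no violence.

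Report the unadjusted model as a sensitivity analysis, and state that the adjusted odds ratio is conditional on the covariates and so not numerically comparable with the unadjusted one. If an SAP already fixes the list, align the article's wording with it.

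The cost is about one sentence, using data already collected. The price is a conditional odds ratio to explain and a rule for the few men whose baseline IPV answer may be missing.
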